### Power considerations and statistical analysis

The primary outcome is the difference in the COMI between the study groups, 12 months after surgery. A difference of two points is considered clinically meaningful [44]. With an assumed SD of 2.5, the effect size of this difference, quantified as Cohen’s *d* is 0.80. Inclusion of 42 patients per intervention group will yield a power of 0.95 at a type-I error rate of 0.05. In addition, 42 patients with low pain catastrophizing scores will undergo the same assessments, but not receive any intervention besides care as usual. Taking into account a drop-out rate of 15%, 150 patients will be included in total.

Baseline patient characteristics will be stratified by group and presented as mean and standard deviation (SD), median and first and third quartile, and count and percentage, as appropriate. Differences in baseline characteristics between randomized groups will not be statistically tested, whereas differences with the separate control cohort will be tested using the independent-samples t-test for continuous variables, and Pearson’s chi-square test for categorical variables. In case of expected cell counts of less than 5, Fisher’s Exact test will be used instead.

All patients randomized (i.e. those with a PCS score > 24) will be analyzed in an intention-to-treat analysis. To test for a difference between the CBT and control group in the COMI at 12 months, linear regression will be used, with correction for baseline COMI and center. In addition, the difference in the trajectory of COMI over time will be assessed by means of linear mixed-effects regression, taking all follow-up measurements into account. Adjustment for center, type of surgery, age and gender will be made and, if necessary, for other prognostic variables significantly associated with the outcome (i.e., acute postoperative pain intensity, severity of catastrophizing, preoperative depression, preoperative surgical fear, length of current sick leave, pain duration). Stepwise backward elimination using the Wald test will be used to select prognostic variables significantly associated with the outcome. Any control variables that are incomplete will be imputed if the proportion of incomplete patients exceeds 0.05. We will use multiple imputation with fully conditional specification with the number of imputations set to the percentage of incomplete patients. Predictive mean matching will be used to draw values to be imputed. Secondary outcome variables will be analyzed similar to the primary outcome. For these, logistic regression analysis adjusted for center will be used to test for differences in proportions at 12 months postoperatively.

Exploratory, we will compare the outcomes of the patients in the two intervention groups with the outcomes of patients with low pain catastrophizing scores (i.e. those with a PCS score < 24) undergoing care as usual. Linear mixed-effects regression for the three groups will be performed with primary and secondary outcomes at the three postoperative assessment periods and controlling for preoperative values. This analysis will indicate whether high catastrophizing patients follow a similar trajectory of pain and functioning after spinal fusion surgery compared non-catastrophizing patients.

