## Abstract

**Background:**

Around 20% of patients undergoing spinal fusion surgery have persistent back or leg pain despite surgery. Pain catastrophizing is the strongest psychological predictor for chronic postsurgical pain. Psychological variables are modifiable and could be target for intervention. However, randomized controlled trials evaluating the effectiveness of psychological interventions to reduce chronic pain and disability after spinal fusion in a population of patients with high preoperative pain catastrophizing scores are missing. The aim of our study is to examine whether an intervention targeting pain catastrophizing mitigates the risk of chronic postsurgical pain and disability. Our primary hypothesis is that targeted perioperative cognitive behavioral therapy decreases the risk of chronic postsurgical pain and disability after spinal fusion surgery in high catastrophizing patients.

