### Participants and recruitment

Adult patients who are undergoing surgery for a degenerative condition of the lumbar spine (lumbar spinal stenosis, spondylolisthesis or degenerative disc disease) using any kind of surgical decompression (laminectomy, hemilaminectomy, foraminotomy, with open or minimally invasive technique) associated with fusion, and able to read and speak Italian (site in southern Switzerland) or Dutch (site in the Netherlands) will be eligible for inclusion. One hundred and fifty patients will be enrolled at the outpatient clinic of the Department of Neurosurgery, Neurocenter of Southern Switzerland, Regional Hospital of Lugano, Lugano, Switzerland (Site 1) and the Department of Neurosurgery of Zuyderland Medical Center, Heerlen, The Netherlands (Site 2). All patients entering the screening phase will be registered on a Patient Registration Log and a unique registration number will be assigned. Clinical data will be assessed to evaluate a subject’s eligibility.

Patients will be excluded from the study if they meet any of the following criteria:
Plans to undergo major surgery within six months after current lumbar spinal fusion surgeryComorbid severe psychiatric conditions such as schizophrenia or personality disorderKnown or suspected non-compliance, drug or alcohol abuseInability to follow the procedures of the study, e.g. due to dementiaThe presence of any serious medical comorbidity such as sepsis or cancer that might cause disability or worsen the patient’s general health conditionPregnancyAn opioid intrathecal pumpPrisoners

Patients eligible for participation will be evaluated at least 6 weeks before surgery and asked for informed consent, and then to complete the PCS [23]. Patients with high pain catastrophizing, defined as a score of ≥24 on the PCS, will be eligible for randomization to perioperative treatment with CBT or educational program. This cut-off was initially based on a previous study in whiplash patients that showed that a pretreatment score of 24 or higher on the PCS best predicted follow-up pain ratings and work status after multidisciplinary treatment [24]. More recently, Tuna et al. [16] suggested an almost identical cut-off for the PCS (i.e. > 24) to obtain the highest sensitivity and specificity to predict unfavorable outcome after spine surgery, defined by as score on the Oswestry Disability Index (ODI) of 20 or higher.

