### Randomization

A computer-generated randomization will be used to allocate the participant to either CBT or educational program with a 1:1 allocation. We will use block randomization stratified by center, with block sizes of 6. The randomization is performed by the Principal Investigator per site, who is not blinded for group assignment. The patients will be randomized immediately after they are included and have completed the PCS (one of the baseline assessments) to be able to make two pre-operative appointments with the patients in the intervention and control group.

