There are some limitations of our study protocol that should be mentioned. The main limitation is patient’s compliance to the intervention. In fact, very few data exist that analyze the impact and feasibility of CBT in the perioperative period after spinal fusion surgery. Another possible limitation is related to potential differences in levels of catastrophizing between the populations of the two centers. Moreover, the exact proportion of high catastrophizing patients (defined in this study as having a PCS ≥ 24) is not known in advance and could vary between the two centers. Additionally, a potential weakness of our study protocol is related to the control condition, conceived to reduce patient’s expectation bias, augmenting contact time and attention, and therefore reducing non-specific effects on outcome. It is well known in psychological research that expectation is one of the most important non-specific factors that may modulate patients outcomes [61]. However, it is difficult to know if this intervention will control for other non-specific factors that could be present (e.g. patient motivation or the therapeutic relationship between the psychologist and patients during CBT). Additionally, because of the difference in length of sessions between the CBT sessions and the education program (the latter being of a shorter duration) the factor of ‘contact time’ is not perfectly controlled for. On the other hand, the first educational session and post-discharge educational session will be held ‘face to face’ whereas all CBT sessions will be delivered by video teleconference. This ‘in-person attention’ in the two educational sessions might compensate for the shorter contact time in the control group in comparison to the CBT group.

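### The primary 12-month COMI model leaves out baseline PCS, which every randomised patient has before allocation; forcing it in would be a nearly free, probably small gain in precision

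*Protocol article*

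**What the plan says.** All points are in the protocol article.

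- **Primary model.** Under Power considerations and statistical analysis, the arms are compared on COMI at 12 months, and "linear regression will be used, with correction for baseline COMI and center". No other covariate is named in that sentence.
- **Where PCS appears.** The next sentence introduces a linear mixed model for the COMI trajectory. After it comes an adjustment sentence with fixed terms (center, type of surgery, age, gender) and a list to be used if needed: "acute postoperative pain intensity, severity of catastrophizing, preoperative depression, preoperative surgical fear, length of current sick leave, pain duration". Then: "Stepwise backward elimination using the Wald test will be used to select prognostic variables significantly associated with the outcome". Whether these two sentences also govern the 12-month regression is not said.
- **Timing of PCS.** Under Randomization: "The patients will be randomized immediately after they are included and have completed the PCS". Under Participants and recruitment: "Patients with high pain catastrophizing, defined as a score of ≥24 on the PCS, will be eligible for randomization". The score is therefore known for everyone randomised.
- **Prognostic role.** The Abstract says: "Pain catastrophizing is the strongest psychological predictor for chronic postsurgical pain". The Background section adds that high preoperative scores go with worse pain and disability at 6 and 12 months after spine surgery.
- **Balance.** Randomisation is stratified by center only, in blocks of 6.

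**The concern.** The trial is built on the premise that catastrophizing drives outcome after fusion. Its severity is measured on a continuous scale before allocation, with no missing values by design. A covariate of that kind is a natural choice for prespecified adjustment, yet the primary model does not contain it.

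The unclear reach of the candidate list makes this worse. If the list does not apply to the 12-month model, PCS is absent from it. If it does apply, PCS enters the primary analysis only when a Wald test on the trial's own data keeps it. It would then compete with acute postoperative pain, which Table 2 schedules four days after surgery. That is after randomisation and after the preoperative CBT sessions.

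What is at stake is the width of the interval around the primary estimate. The Discussion intends to draw consequences from a null result as well as from a positive one, so the interval matters beyond the significance test. Adding PCS after the results are known would be open to challenge; adding it now is not.

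**Working it through.** **Inputs from the protocol article:** target difference 2 COMI points, SD 2.5, 42 evaluable patients per arm, type I error 0.05, 15% dropout, 150 patients in total over three groups.

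**Assumed, because the documents give no figure:** the partial correlation r of baseline PCS with 12-month COMI, given baseline COMI and center, among patients with PCS of 24 or more. Range used: 0.1 to 0.3.

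**1. Reproduce the stated power.** Effect size 2/2.5 = 0.80. SE = 2.5 × √(2/42) = 0.546. A two-sided two-sample t-test (noncentral t, 82 degrees of freedom) gives power 0.952, against the stated 0.95. Dropout: 42/0.85 = 49.4, so 50 per group, and 3 × 50 = 150. Both figures reproduce with no covariate counted, so the sample size does not depend on PCS.

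**2. Add PCS.** The residual SD is multiplied by √(1 − r²), and one degree of freedom is spent. Taking 2.5 as the residual SD before PCS:

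| r | SE | fall in SE | power for 2 points | patients per arm for the same precision, 42(1 − r²) |
|---|---|---|---|---|
| 0 (planned model) | 0.546 | – | 0.952 | 42 |
| 0.1 | 0.543 | 0.5% | 0.954 | 41.6 |
| 0.2 | 0.535 | 2.0% | 0.959 | 40.3 |
| 0.3 | 0.520 | 4.6% | 0.967 | 38.2 |

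**3. Allow for what baseline COMI already explains.** The value 2.5 is the SD in the power calculation, which makes no reduction for covariates. If baseline COMI correlates 0.5 with the outcome (assumed), the residual SD is 2.5 × √0.75 = 2.17 and the SE without PCS is 0.472. Power for 2 points is then 0.987 without PCS, and 0.988 (r = 0.1) to 0.992 (r = 0.3) with it. The SE at r = 0.3 is 0.451. The percentage fall is the same; the absolute gain is smaller.

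**4. Range restriction.** Only scores of 24 or more are randomised. If the SD of PCS shrinks to a fraction u of its full-range value, the correlation becomes r·u/√(1 − r² + r²u²). For a full-range r of 0.4 and u of 0.5 to 0.7 (both assumed), this gives 0.21 to 0.29, before baseline COMI takes its share. That is why the range above stops at 0.3.

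**5. Chance imbalance.** With SD 2.5, chance differences in PCS between the arms contribute a component with SD r × 0.546 to the estimate. At r = 0.3 this is 0.164, a 95% range of ±0.32 points. It is not a second loss on top of step 2: 0.520² + 0.164² = 0.297, which is 0.546² up to rounding (0.298). The SE without PCS already contains it.

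**The case against.** The strongest case against raising this is that nothing in the primary model is wrong. It is prespecified and contains the baseline value of the outcome and the only stratification factor. The stated power reproduces without any covariate gain. All of that stands.

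Three stronger readings are tempting, and the documents support none of them.

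- **That the omission biases the result or weakens the test.** It does not. Under 1:1 randomisation the estimate is unbiased and the type I error valid without PCS. A chance imbalance in one trial is part of the sampling variability that the standard error already reflects.
- **That the protocol establishes a large gain.** The strongest-predictor statement concerns chronic postsurgical pain, not COMI. The 12-month association in the Background comes closer, since COMI covers pain and disability, but no coefficient is given and nothing is conditioned on baseline COMI. The evidence cited for the cut-off concerns discrimination around a score of about 24, and everyone randomised is already at or above it.
- **That the Discussion admits the problem.** Its limitation on "potential differences in levels of catastrophizing between the populations of the two centers" is about differences between centers. Stratification by center and the center term deal with those; the remark says nothing about imbalance between arms.

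It can also be said that PCS is already on the adjustment list. That is true, but the list is optional, driven by the data, and of unclear reach for the 12-month model. A planned route to adjustment for PCS exists; a fixed one in the primary analysis does not.

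**Conclusion.** The point holds as an improvement in precision, not as an error. The primary 12-month regression adjusts for baseline COMI and center only, although baseline PCS is complete before allocation and the protocol itself treats it as prognostic. The wording leaves open whether the stepwise list reaches that model.

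The gain is likely to be small: a standard error lower by about 0.5% to 4.6%, and power for 2 points of about 0.954 to 0.967 instead of 0.952. This rests on an assumed partial correlation of 0.1 to 0.3 within the restricted PCS range and on 2.5 as the residual SD. The absolute gain shrinks further if baseline COMI explains part of the outcome. No stated figure fails and no conclusion of the trial is endangered. The case for the change is that it costs almost nothing and settles an ambiguity in the primary analysis.

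**What to change.** Define the primary model as 12-month COMI on arm, baseline COMI, center and baseline PCS, with PCS continuous and forced in without selection. State in the same place that the backward-elimination list does not apply to this model. Make the change before outcomes are compared by arm.

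The cost is one degree of freedom out of about 80. No new data and no imputation of PCS are needed, and the sample size stays as it is.

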#### Primary outcome

The primary outcome is the patient’s score on the COMI 12 months after surgery. The COMI is a self-administered multidimensional instrument that consists of seven items which assess the extent of the patient’s back pain and leg pain, difficulties with functioning in everyday life, symptom-specific well-being, general quality of life, and social and work disability. Leg pain and back pain are assessed on 0–10 graphic rating scales and all other items on 5-point adjective scales. In each case, a higher score indicates worse status [28]. The instrument is validated in Italian and Dutch [29, 30].

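### The supportive mixed model of COMI does not name baseline COMI, selects covariates on the trial's own data, and allows a post-randomization covariate; the primary regression is unaffected

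*Protocol article*

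**What the plan says.** All of this stands in the protocol article, section on power considerations and statistical analysis, unless another section is named.

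- **Primary test.** "The primary outcome is the patient’s score on the COMI 12 months after surgery" (Primary outcome section). It is tested by linear regression corrected for baseline COMI and center. No covariate is selected from the data.
- **Additional mixed model.** The COMI trajectory is compared between the randomized groups using all follow-up measurements. The covariate sentence that follows reads: "Adjustment for center, type of surgery, age and gender will be made and, if necessary, for other prognostic variables significantly associated with the outcome". Six candidates are then listed: acute postoperative pain intensity, catastrophizing severity, preoperative depression, surgical fear, sick-leave length and pain duration.
- **Selection rule.** "Stepwise backward elimination using the Wald test will be used to select prognostic variables significantly associated with the outcome". No removal threshold is given.
- **Secondary outcomes.** They are to be handled in a similar way to the primary outcome. For proportions, "logistic regression analysis adjusted for center will be used to test for differences in proportions at 12 months postoperatively".
- **Exploratory three-group mixed model.** It does control for preoperative values.
- **Timing.** Table 2 places the early postoperative pain rating at day 4. Randomization follows the PCS at enrollment, and two CBT sessions come before surgery (Randomization; Cognitive behavioral therapy).

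**The concern.** Three features of the mixed model deserve attention.

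1. Baseline COMI is named in the model described before it and in the three-group model described after it, but not here. The baseline value usually predicts follow-up strongly. Without it, group differences at a visit, or averaged over visits, are less precise and keep any chance baseline imbalance. They could then disagree with the primary regression for no substantive reason.
2. Covariates are kept or removed by their significance in the same data that estimate the treatment effect. The final standard error takes no account of that search.
3. One candidate is not a baseline variable. Acute postoperative pain arises after randomization and after the preoperative CBT sessions, and the Discussion argues that starting treatment before surgery might reduce it. Conditioning on it can take out part of the effect the trial is meant to measure. The Background lists it among the most important predictors of chronic pain, so a significance rule may well retain it.

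**Working it through.** **Step 1. The plan's own figure.** Inputs: a target difference of 2 points and SD 2.5, hence d = 2/2.5 = 0.80, and 15% dropout. The claim to reproduce is "Inclusion of 42 patients per intervention group will yield a power of 0.95 at a type-I error rate of 0.05", with 150 enrolled over the three groups.

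- n per arm = 2(1.96 + 1.645)² / 0.80² = 40.6, so 41. With 42 per arm the two-sided t-test power is 0.952.
- 42 / 0.85 = 49.4, so 50 per group, and 3 × 50 = 150.

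The sample size reproduces and does not depend on the mixed model.

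**Step 2. Baseline adjustment, one visit.** The baseline-to-follow-up correlation r is not in the documents; 0.3 to 0.5 is assumed. Residual variance is multiplied by 1 − r². The unadjusted standard error is 2.5 × √(2/42) = 0.546.

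| r | variance removed | standard error | equivalent n, 1/(1 − r²) |
|---|---|---|---|
| 0.3 | 9% | 0.520 | × 1.10 |
| 0.4 | 16% | 0.500 | × 1.19 |
| 0.5 | 25% | 0.472 | × 1.33 |

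**Step 3. Baseline adjustment in a mixed model.** Assumed: SD 2.5, correlation 0.5 between all pairs of baseline, 2, 6 and 12 months, 42 per arm, complete data, 60 simulated trials.

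- Group difference averaged over visits: mean standard error 0.442 without baseline and 0.351 with it. (0.351/0.442)² = 0.63, a variance cut of about 37%.
- Group-by-time term (12 versus 2 months): standard error 0.539 both ways, with identical estimates. A baseline covariate shifts all of a patient's visits equally and cancels from within-patient change.

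So the cost depends on which parameter is tested, and the article names only a difference in trajectory.

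**Step 4. Backward elimination.** Simulation under no treatment effect: 42 per arm, four forced covariates, six candidates, removal at p > 0.05 (assumed), ordinary regression on one follow-up score as a simplified stand-in for the mixed model.

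| Situation | after selection | full set, no selection |
|---|---|---|
| Candidates prognostic (assumed coefficients 0.1 to 0.3) | 0.057 to 0.071 | 0.047 to 0.053 |
| No candidate prognostic | 0.045 to 0.060 | 0.043 to 0.057 |

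At 8,000 simulated trials the Monte Carlo standard error is about √(0.06 × 0.94 / 8000) = 0.003. A separate run of 10,000 null trials with two prognostic candidates out of six gave 0.057 with selection and 0.048 with a prespecified set.

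**Step 5. Acute postoperative pain as a covariate.** In an assumed example where CBT lowers early pain and early pain worsens outcome:

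- true total effect −0.62 SD: estimated as −0.49 after selection, a loss of 0.13/0.62 = 21%;
- true total effect −0.70 SD: estimated as −0.50, a loss of 0.20/0.70 = 29%.

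These show direction and plausible size. The documents give no figures for either path.

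**Step 6. Logistic models with center only.** Type I error in simulation was 0.044 to 0.048, so there is no inflation. At an assumed treatment log odds ratio of 1.2, power without versus with a prognostic covariate of log odds ratio 0.5, 1.0 or 1.5 per SD was 0.70 vs 0.71, 0.60 vs 0.66 and 0.47 vs 0.60.

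**The case against.** The strongest reply is that the confirmatory test is untouched: it is prespecified with baseline COMI and center, and the trial is powered on that comparison. This stands. A reader might infer that the trial's primary error rate is distorted; the text does not support that.

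Second, the missing baseline is read from a list in a condensed article. The covariate sentence could be meant to add to the correction already named for the primary regression. This stands in part: the accurate statement is that baseline COMI is not named, not that it is certainly excluded. However, the sentence repeats center, which makes it read as a self-contained list, and the three-group model names the preoperative value explicitly.

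Third, if trajectory means a group-by-time term, leaving out baseline costs nothing (Step 3). That is correct. But the modeled visits start at 2 months and CBT ends 4 to 8 weeks after surgery, so an effect already present at 2 months and then maintained would not show in that term. The informative contrasts are at visits or averaged over them, where baseline matters.

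Fourth, a reader might infer that every secondary endpoint gets its own selected covariate set. That is a plausible reading of the instruction to analyze them similarly, but it is not stated; the same words could mean regression on the baseline value and center. A reader might also fault the center-only logistic models as invalid. They are valid and only less efficient, and a further covariate would change the odds ratio to a more fully conditional one.

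**Conclusion.** The point holds for the additional mixed model and should be corrected there. The selection step and the post-randomization candidate are explicit in the text; the missing baseline is an inconsistency with the models on either side of it.

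The sizes are moderate. Type I error is about 6-7% instead of 5% when candidates are prognostic, given a 0.05 removal threshold that the article does not state and a simplified single-visit simulation. The variance reduction forgone is 9-25% for a single-visit contrast at r = 0.3 to 0.5, about 37% for the visit average at r = 0.5, and nil for a pure group-by-time term. Acute postoperative pain is the clearest source of bias: its direction follows from the trial's own rationale, while its size rests on assumed effects. The primary analysis and the sample size are not affected.

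**What to change.** - Delete the backward elimination.
- Prespecify one covariate set for the mixed model: baseline value of the outcome, center, type of surgery, age, gender, and any of the listed pre-randomization variables named in advance. Use the same set for secondary outcomes analyzed this way.
- Remove acute postoperative pain intensity from the covariates.
- State which parameter the trajectory comparison tests.
- Optional, for efficiency only: add the baseline value to the logistic models and say that the odds ratio is then conditional on it.

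The cost is wording in the analysis plan and a few degrees of freedom among 84 planned analyzable patients. No new data are needed.

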### Comparators

#### Cognitive behavioral therapy

The CBT protocol was specifically developed for the present study by a team of psychologists with longstanding experience in the treatment of chronic pain patients. The intervention consists of six sessions, individually delivered by clinical video teleconferencing, and specifically aiming to reduce pain catastrophizing [25]. Two sessions are delivered before surgery (resp. at 3–6 weeks and 1–3 weeks pre-surgery) and four sessions after surgery. The four post-surgical session will start approximately 2 weeks after surgery, with sessions spaced one week apart (allowing a range of 2–3 weeks to prevent scheduling difficulties). All sessions have a duration of 60 min except for the first session that will take 90 min. Details of timing and the content of each sessions can be found in Table 1. In short, sessions focus on pain education, identifying, challenging and replacing catastrophizing thoughts, discussing fears of surgery, activities and goals after surgery, consequences of avoidance behavior, adaptive means for accomplishing interpersonal needs and relapse prevention. It also includes progressive muscle relaxation (PMR) training to provide patients with tools to cope with acute postoperative symptoms and to enhance their feelings of control. The protocol is manualized and the therapists delivering the treatment record after each session which components have been addressed. Patients receive a workbook consisting of a brief summary of the pain education, and for each session an explanation of the exercises for that week, several pages with forms to fill in and some examples. The homework is sent to the therapist before the start of the next session. Patients also receive an audio file with a recording of the PMR exercise that they are requested to practice at least once a day.

**Table 1 Tab1:** timing and content of cognitive behavioral therapy sessions

Timing	Aim	Content

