It should be noted that none of the above studies preselected patients based on a psychological high-risk profile (i.e. high pain catastrophizing or anxiety/fear) despite the fact that at least some of these interventions were specifically designed to reduce these risk factors. Lotzke et al. speculated that their null finding may have been due to the high degree of variability in fear-avoidance beliefs in their patients [59]. Therefore, they recommended that future studies should evaluate the effects of psychological treatment specifically in patients with a high psychological risk profile for poor outcome.

In line with this recommendation, a crucial aspect of the current study is that we will offer CBT specifically to patients reporting high levels of pain catastrophizing. Another feature, which sets out study protocol apart from most previous studies in this area, is the inclusion of an active control intervention consisting of an educational and progressive exercising program. This allows us to assess the effect of CBT per se and control for non-specific effects such as expectancy, contact time and attention. In addition, starting treatment before surgery may be expected to lead to more profound intervention effects than post-surgical intervention only, because it might decrease early postoperative pain, which is among the most prominent predictive factors for developing CPSP [60]. Finally, we aim to assess the meaningfulness and clinical usefulness of the perioperative CBT intervention by comparing the outcomes of the high PCS/CBT group not only with the control group, but also to the outcomes of the low risk group (i.e. PCS score < 24). This offers the possibility to examine whether CBT can reduce the negative effects of catastrophizing on outcome to the level of improvement one would expect in non-catastrophizing patients.

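### The extended adjusted COMI model may adjust for acute postoperative pain, which is measured after randomisation and which pre-surgical CBT is meant to lower

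*Protocol article*

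**What the plan says.** All references are to the protocol article.

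- **Primary test** (Power considerations and statistical analysis). For COMI at 12 months, "linear regression will be used, with correction for baseline COMI and center".
- **Second COMI analysis** (same section). Next, "the difference in the trajectory of COMI over time will be assessed by means of linear mixed-effects regression", using all follow-up visits. The sentence after it adjusts for center, type of surgery, age and gender and, where needed, "for other prognostic variables significantly associated with the outcome (i.e., acute postoperative pain intensity, severity of catastrophizing" and four further variables.
- **Selection rule** (same section). "Stepwise backward elimination using the Wald test will be used to select prognostic variables significantly associated with the outcome".
- **Randomization.** "The patients will be randomized immediately after they are included and have completed the PCS". This happens before surgery.
- **Cognitive behavioral therapy.** "Two sessions are delivered before surgery (resp. at 3–6 weeks and 1–3 weeks pre-surgery) and four sessions after surgery". Relaxation training is included "to provide patients with tools to cope with acute postoperative symptoms".
- **Table 2.** The only assessment in the first days after surgery is the pain NRS at day 4, listed under secondary outcomes.
- **Discussion.** Starting treatment before surgery is expected to work better than postoperative treatment alone "because it might decrease early postoperative pain, which is among the most prominent predictive factors for developing CPSP".

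**The concern.** The protocol gives one measurement two incompatible roles. In the Discussion, early postoperative pain is a route by which CBT is expected to work. In the analysis section, it is a prognostic factor to be adjusted away.

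A covariate recorded before randomisation cannot be changed by treatment, so adjusting for it leaves the intended effect intact. Early pain can be changed by treatment. Adjusting for it compares CBT and control patients who had the same early pain, which takes out whatever benefit came through lower early pain. It also undoes part of the balance that randomisation created. If CBT lowers early pain, CBT patients with a given day-4 score tend to be those otherwise prone to more pain, and they are set against control patients who are less so.

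At stake is the reading of the mixed-effects analysis, which is the COMI comparison of the two randomised arms that uses every follow-up visit. If it showed a smaller difference than the primary regression, a reader could not tell whether the effect differs between visits or had been adjusted away.

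**Working it through.** **1. Order of events.** Randomisation takes place at enrollment, at least 6 weeks before surgery. CBT session 1 is 6–3 weeks and session 2 is 3–1 weeks before surgery. Surgery follows, then the NRS at day 4. Session 3 comes 1–3 weeks after surgery (Table 1). The day-4 score therefore follows randomisation and exactly two CBT sessions. That the listed variable is the day-4 NRS is inferred from Table 2, but any measure of acute postoperative pain would come after randomisation.

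**2. The plan's own figures.** Inputs: difference 2, SD 2.5, 42 per arm, two-sided alpha 0.05 (sidedness is not stated).
- Standard error = 2.5 × √(2/42) = 0.546. Then 2/0.546 = 3.67, and 3.67 − 1.96 = 1.71, so power is 0.956. The noncentral t gives 0.952. The stated 0.95 is reproduced.
- 42/0.85 = 49.4, rounded up to 50; 3 × 50 = 150. The stated total is reproduced.

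These figures belong to the 12-month comparison and are not in dispute.

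**3. Size of the shift.** In a linear model,

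adjusted difference = total difference − a × b,

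where a is the amount by which CBT lowers day-4 NRS and b is the within-arm slope of COMI on day-4 NRS. With r the within-arm correlation, b = r × SD(COMI)/SD(NRS). The documents give neither a, r nor SD(NRS). Assumed: SD(NRS) 2.5, a from 0.5 to 1.5, r from 0.2 to 0.5. With SD(COMI) 2.5, b = r. For a total difference of 2 points the adjusted difference (and share removed) is:

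| a | r = 0.2 | r = 0.3 | r = 0.5 |
|---|---|---|---|
| 0.5 | 1.90 (5%) | 1.85 (7.5%) | 1.75 (12.5%) |
| 1.0 | 1.80 (10%) | 1.70 (15%) | 1.50 (25%) |
| 1.5 | 1.70 (15%) | 1.55 (22.5%) | 1.25 (37.5%) |

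At a = 0 nothing is removed. Reading the removed share as the part of the effect that runs through early pain also requires that early pain and late COMI have no unmeasured shared causes.

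**4. Chance that the variable is retained.** For a single covariate in 84 patients with Wald p < 0.05, b divided by its standard error is about r × √81/√(1 − r²).
- r = 0.2: 1.84, chance about 0.45
- r = 0.3: 2.83, chance about 0.81
- r = 0.5: 5.20, chance about 1.0

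These are rough values. Other covariates in the model and the use of several visits would change them.

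**5. Which contrasts move.** Entered as a main effect, a day-4 score is constant within a patient. With complete data and a random intercept it cancels from within-patient changes, so the group-by-time interaction is unchanged. A simulated check with three follow-ups found agreement to within 1e-13. The average group difference and the differences at each visit do move.

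**The case against.** The strongest reply is that the confirmatory result is untouched. The 12-month regression is written with baseline COMI and center, and the longer covariate list comes only after the mixed-effects model has been introduced. That stands. A reader might infer that the primary test is biased, but the text does not support this, although it does not expressly confine the extended adjustment to the mixed model.

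The problem is also conditional. Extended adjustment is made only where needed, the variable must survive elimination, and the Discussion says only that CBT might lower early pain. This stands too, so a loss of effect is a risk and not a certainty.

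If trajectory means the group-by-time interaction alone, step 5 shows no change with complete data. This narrows the point to average and visit-specific differences.

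It is tempting to say that every secondary outcome is biased. The plan analyses them in the manner of the primary outcome, and proportions by logistic regression adjusted for center. Only models that carry the extended adjustment are exposed.

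It is equally tempting to quote a fall from the planned power of 0.95. That figure is for the 12-month comparison. The protocol claims no power for the mixed model, and no mediation effect is documented, so a loss of power cannot be stated.

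None of this removes the contradiction: the plan permits adjustment for a variable that its own rationale expects treatment to change.

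**Conclusion.** The point holds for the extended adjusted model. As written, the selection rule can bring a post-randomisation variable on the stated treatment pathway into the COMI mixed-effects model. If that happens and CBT lowers early pain, the adjusted average and visit-specific differences are not total intention-to-treat effects and probably understate the benefit. The same applies to any secondary-outcome model with the same adjustment.

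The size cannot be derived from the documents. The 5% to 38% of a 2-point effect rests on the assumed NRS SD, CBT effect and correlation in step 3 and only illustrates the order of magnitude. The primary 12-month regression and its sample size are unaffected as written.

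**What to change.** In the analysis section:

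1. Delete acute postoperative pain intensity from the candidate covariates.
2. State that only variables recorded before randomisation may be adjusted for, and that severity of catastrophizing means the baseline PCS. The list gives it no time point, although the Randomization section calls the PCS a baseline assessment.
3. If early pain is of interest, report the day-4 NRS by arm as a secondary outcome, where Table 2 already places it, or use it in a separate mediation analysis labelled as such.

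The cost is a sentence or two before the data are analysed. No visits, patients or data are added.
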